#### Withdrawal of participants

Further power calculations suggest that if any cafeterias drop out then *n* = 14 cafeterias would detect an effect size of 8%, *n* = 11 for 9%, and *n* = 10 for 10%.

### Randomisation

After all the sites had agreed to participate, randomisation was performed by a blinded statistician (MP) who allocated a list of anonymised site names using the rank of random numbers from Excel.

### Measures

#### Primary outcome

Total energy (kcal) purchased from intervention food categories per day, calculated from the total number of units sold of each individual product within an intervention food category and the total number of calories contained in each of these products. Sales data are recorded using electronic tills every day of operation during the trial. These data are then sent electronically to the study team.

#### Secondary outcomes

i.Total energy (kcal) purchased per day from
non-intervention categories, andall food and drink products.
ii.Total revenue

This is calculated from the number of units of each individual product sold in the cafeterias and the price of each of these products. These data will be collected using the electronic tills for every day of operation during the trial.

#### Covariates

Analyses (with the exception of those examining revenue) will control for the total number of daily transactions to take account of footfall. Transactions are defined as the number of unique payments to purchase products in the cafeteria.

Further variables may include the catering company serving the distribution centre, the day of the week, weather conditions at the location (daily mean temperature, daily hours of sunshine, and daily rainfall), whether calorie information is displayed for the products on offer, and notable events (e.g., a workplace party) that may affect sales.

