In terms of interventions targeting portion sizes, there is substantial experimental evidence that portion size reductions reduce selection and consumption of food [22, 23]. The Cochrane review that investigated size interventions included 69 studies in food, estimating that consistently reducing portion sizes could reduce energy intake by up to 16% in UK adults [13]. It also highlighted some key outstanding uncertainties, in particular the relative absence of evidence from real-world settings and over sustained time periods. One concern with the real-world application of this intervention is that customers are more likely to choose larger portions when larger options are available, thereby potentially undermining this intervention if changes are not applied to every available product. A further concern is that consumers may compensate by purchasing more products if they perceive that their portion is too small. Some evidence suggests that, contrary to a compensatory mechanism, portion size reductions may change related norms, leading consumers to purchase smaller food items in the future [24, 25], but it is unclear if this effect is generalisable; particularly to those with physically tiring jobs. A recent pilot trial in six worksite cafeterias reduced the portion size of main meals, sides, desserts, and cakes by approximately 10–15%, which led to a statistically non-significant but numerical reduction in energy purchased from intervention categories of approximately 8% [17]. However, larger field trials that recruit more sites and test interventions for longer periods of time are needed to provide more precise estimates for the effectiveness of both availability and portion size interventions.

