#### Blinding

Cafeteria staff will be aware of the nature of each intervention to enable the implementation of the interventions. Customers will be told via posters that a health initiative is being implemented to improve the healthiness of the food and drink on offer in the cafeteria. They will not be informed about the actual changes.

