## Discussion

This study will provide the most reliable estimate to date in real-world settings (namely worksite cafeterias) of the effect sizes of two promising interventions for reducing energy purchased: increased proportion of lower energy foods available for selection, assessed on its own and in combination with reduced portion sizes. It builds on the results of two previous pilot studies suggesting that when implemented individually, increasing the proportion of healthier foods available could reduce energy purchased by 7% and reducing portion sizes by about 10% could reduce energy purchased by 9%, although the latter effect was not statistically significant [17, 18].

These interventions have the potential not only to tackle overweight and obesity in the workplace, but also to reduce inequalities in health due to higher rates of overweight and obesity in more deprived populations ([27]; Public Health [28]). The majority of employees that use the cafeterias included in the current study work in manual and/or unskilled roles. If this study demonstrates that these interventions can reduce energy purchased amongst such a group, which is at higher risk for ill health associated with obesity, then these interventions may be viable options for government policies to reduce ill health equitably [29].

One limitation of the current approach is that the primary outcome is estimated from sales data. While this outcome provides reliable data on sales, it is an imperfect measure of energy actually consumed. Energy consumed from other sources while at work – such as from vending machines or from food brought from home – will not be captured. It is also does not account for the incomplete consumption of food and drink purchases.

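### Every energy analysis adjusts for same-day transactions, which the interventions may change, so the estimate is energy at a given number of payments rather than the total daily energy named as the outcome

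*Protocol article*

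**What the plan says.** The Primary outcome section of the protocol article defines a daily total: "Total energy (kcal) purchased from intervention food categories per day". The secondary energy outcomes take the same form, "Total energy (kcal) purchased per day from" non-intervention categories and from all products. The hypotheses at the end of the Background are also about totals: fewer calories purchased under Availability than at baseline, and fewer again once Size is added.

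The Covariates section then states: "Analyses (with the exception of those examining revenue) will control for the total number of daily transactions to take account of footfall". This is a fixed commitment; catering company, weekday, weather and the other variables listed there are only possible additions. The same section gives the definition: "Transactions are defined as the number of unique payments to purchase products in the cafeteria". The count therefore covers the whole cafeteria, is taken on the same day as the outcome, and counts payments rather than items or people.

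The article names no energy analysis without this covariate. It does not list transactions as an outcome, and it does not say that its target is energy at a given footfall.

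**The concern.** A covariate measured after the intervention has started is harmless for a total effect only if the intervention does not move it. Here there are plausible routes by which it could. Availability removes higher-energy products, where possible the highest. Size shrinks portions, with a matching price change requested. The Blinding section adds that "Customers will be told via posters that a health initiative is being implemented to improve the healthiness of the food and drink on offer". Each of these could change how often workers pay at the till.

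Daily energy is the number of payments multiplied by energy per payment. Holding the first factor fixed leaves roughly the second, whereas the outcome and hypotheses describe the product. If payments shift, a result reported as a change in total energy purchased would be a different quantity. The error could go either way: extra separate payments would make the adjusted fall larger than the total fall, and lost custom would make it smaller. As no direct analysis of transactions is named, a reader could not tell which had happened.

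**Working it through.** **The plan's own figure.** Sample size determination gives SD 0.111 on the log scale, 19 cafeterias, a one-sided 5% test and a detectable fall of 6.5% (0.067 log) at 80% power. Treated as a one-sample t-test on per-cafeteria changes, the noncentrality is 0.067 / (0.111/√19) = 2.63 on 18 degrees of freedom, and power is 81.2%. The stated figure reproduces. The 6.5% serves below as the reference effect.

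**Inputs.** Outcome: daily kcal (Primary outcome). Covariate: daily payments (Covariates). Change in payments caused by the intervention: not in the document, so assumed, from -5% to +5%. Change in energy per payment: assumed at -6.5%, to match the planned effect.

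**Formulae.** Let T be the ratio of payments and P the ratio of energy per payment, intervention to baseline.
- Total effect = T × P - 1.
- Adjusted effect with transactions coefficient b on the log scale = T^(1-b) × P - 1. With b = 1 (energy proportional to payments) this is P - 1, whatever T is.

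**Results with b = 1 and P = 0.935.**

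| Payments | Total effect | Adjusted effect |
|---|---|---|
| -5% | 0.95 × 0.935 - 1 = -11.2% | -6.5% |
| -2% | 0.98 × 0.935 - 1 = -8.4% | -6.5% |
| 0 | -6.5% | -6.5% |
| +2% | 1.02 × 0.935 - 1 = -4.6% | -6.5% |
| +5% | 1.05 × 0.935 - 1 = -1.8% | -6.5% |

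**Without proportionality.** With b = 0.5 and payments +5%, the adjusted effect is √1.05 × 0.935 - 1 = -4.2%, against a total of -1.8%. With payments -5% it is √0.95 × 0.935 - 1 = -8.9%, against -11.2%. About half of the part that runs through payments is removed.

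**Simulation on the trial's schedule.** Daily data for 19 sites over 25 weeks, with the article's roll-out, were fitted with site and week effects, with and without log transactions. The noise values were assumed. Availability estimates:

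| Scenario | Adjusted | Unadjusted |
|---|---|---|
| Payments -5%, energy per payment -6.5% | -6.4% | -11.1% |
| Payments -6.5%, energy per payment unchanged | +0.2% | -6.3% |
| Payments +5%, energy per payment -6.5% | -6.6% | -1.9% |
| Payments unchanged, same-payment compensation leaves energy per payment at -2% | -2.1% | -2.2% |

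In the first three rows the change in payments drops out of the adjusted estimate. In the last, compensation within a payment stays in both.

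**The case against.** Adjusting for footfall has a sound purpose: it removes swings in staffing and attendance that have nothing to do with the intervention. It is also a defensible choice when custom may leak away. If workers turn to other food, cafeteria energy falls although they may eat no less; the unadjusted total counts that as benefit and the adjusted estimate does not. Revenue is analysed without the covariate, so a material loss of custom should show there, though only indirectly because prices and product mix also change. The document gives no evidence that transactions will change. Transactions also include purchases outside the outcome, such as breakfasts and soups, so strict proportionality may not hold. Further models are commonly left to an analysis plan, which is not shown here. All of this stands, and it is why the adjusted model should be kept. It does not remove the mismatch, because the adjustment is a rule the article states, set against an outcome and hypotheses it also states.

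Two stronger readings are tempting and not supported. A reader might infer that the adjustment removes compensatory buying altogether. The Background says: "A further concern is that consumers may compensate by purchasing more products if they perceive that their portion is too small". More products in the same payment raise energy per payment and stay in the estimate, and switching to untargeted items within a payment remains visible in the secondary energy outcomes. Only compensation through a separate payment drops out, and that sentence does not specify one. A reader might also infer that the article itself predicts lost custom. The Discussion mentions energy from other sources, "such as from vending machines or from food brought from home", but as a limit of sales data, not as a response to the interventions.

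**Conclusion.** The point holds in a limited form. The stated rule makes the energy estimates conditional on a post-intervention variable, while the outcome and hypotheses are about total daily energy. If the interventions change the number of payments, the part of the effect that runs through lost custom or extra separate payments is removed: fully under proportionality, partly otherwise.

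For assumed changes in payments of -5% to +5%, with energy per payment down 6.5% and proportionality, the total effect ranges from about -11.2% to -1.8% around an adjusted estimate fixed at -6.5%. The gap is about 4.7 percentage points either way (11.2 - 6.5 and 6.5 - 1.8). These changes are illustrations, not forecasts; if payments do not change, there is no gap. The point is worth acting on because the analyses named in the article would not show directly which case applies.

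**What to change.** Keep the transaction-adjusted model and make three changes.

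1. State that its result is energy conditional on the number of transactions.
2. Analyse daily transactions as an outcome with the same model.
3. Report the energy outcome without the transactions covariate beside the adjusted one, adjusting for site, calendar time and day of week. A footfall measure that the interventions cannot affect, such as staff on site each day, could be added if it is available; the article describes no such measure. A fixed headcount per site would not help, since site effects absorb it.

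Interpret the two energy estimates together with the transactions result. A rule that requires only agreement in direction would not be enough, because lost custom also pushes the unadjusted estimate towards a fall.

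The cost is two further model fits on till data the trial already collects. The unadjusted estimate will be noisier, and the article gives no SD without this covariate from which to say by how much.

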### Additional measures

Demographic characteristics of employees, including age, gender, and occupational status, will be requested for each distribution centre.

Variables relevant to the specific interventions will be recorded, including:

*For the Availability intervention*: proportion of food/drink intervention items that are categorised as healthier pre-intervention; proportion of food/drink items that are targeted by the intervention; mean energy (kcal) per item pre-intervention; reduction (%) in proportion of intervention items that are categorised as less healthy from pre-intervention; reduction (%) in energy (kcal) per item from pre-intervention; mean price pre-intervention; mean change (%) in price.

*For the Size intervention*: mean energy (kcal) per product pre-intervention; mean reduction (%) in energy (kcal) per product; mean price pre-intervention; mean reduction (%) in price.

### Data analysis / statistical plan

Generalised linear mixed models will be used to estimate the potential impact of the Availability intervention and the combined Availability + Size intervention compared to baseline. The primary analysis will determine the effectiveness of these interventions across all sites, with follow up tests to determine if the effect varied across sites. Primary analyses will be on an intention to treat basis (i.e. data will be analysed according to the period that they should be in [baseline, Availability, or Availability + Size], regardless of adherence to the intervention).

Any outliers will be identified using range checks, scatter plots, and histograms. If any outliers (defined as any value that differs from the median by more than 3 standard deviations) are detected then further checks will be performed by the research team to ensure they are not the result of data entry errors. The cafeterias will also be contacted to determine if there were any events that could explain these outliers as genuine or uncharacteristic. Any true outliers will be included in the primary analysis but, if deemed necessary, may be modelled by a factor if there is a regular event, and a sensitivity analysis will be completed without any true outliers to compare the robustness of model results.

Sensitivity analyses will be conducted using a per protocol analysis, i.e. data will be analysed based on adherence to the intervention; intervention categories that have failed to receive sufficient changes will be excluded from the primary outcome. Non-adherence is defined as a failure to make the pre-specified changes to an intervention category in at least 50% of the sites within the intervention week. Checks are performed by a member of the research team visiting the sites to determine whether the sites adhere to the interventions. The pre-specified threshold for intervention adherence (i.e. proportion of less healthy items offered for Availability) within each intervention category is defined in Additional file 1, with at least a 10% reduction by volume in each targeted product required for Size. If a site fails an intervention check for one category during a site visit, but then resolves the issue within the same week (Monday-Sunday), then the site will be recorded as passing that intervention checking.

Due to the nature of the stepped-wedge design it will not be possible to blind the statistician to intervention status while conducting the analysis.

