The proposed study will provide the most reliable estimate to date of the effect sizes of two promising interventions for reducing energy purchased in 19 worksite cafeterias: increased proportion of lower energy foods available for selection, assessed on its own and in combination with reduced portion sizes. The cafeterias are located across Great Britain, serving mainly manual workers, a group with typically poorer diets, as reflected in their higher rates of obesity, type 2 diabetes and associated cancers [4]. Manual workers therefore have more to gain than non-manual workers from effective interventions. Study hypotheses: 1. fewer calories will be purchased during the availability intervention period when compared to the baseline; 2. fewer calories will be purchased during the availability + portion size intervention period when compared to the baseline and when compared to the availability intervention period.

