## Methods

### Study design

A stepped-wedge design (Campbell & Walters, 2014) will be used, with each of the 19 sites randomly allocated to the time at which they implement each of the two interventions across a period of 25 weeks (see Additional file 2). This design was selected over a parallel groups cluster RCT due to insufficient resources to implement the intervention(s) at all sites simultaneously. Weeks 1 to 4 will comprise the minimum baseline period – during which data will be recorded without any intervention – followed by 21 weeks during which interventions will be introduced and maintained. From Week 5 until Week 13, two sites a week will implement the first intervention – Availability. In Week 14, the 19th site will implement this intervention. From Week 13 until Week 21, two sites a week will implement the second intervention – Size – while continuing the Availability intervention. In Week 22, the 19th site will implement this intervention. The interventions will continue until the end of Week 25 for all sites (the duration of the Size intervention in sites will therefore vary between 4 and 13 weeks).

The study was prospectively registered on ISRCTN (10.1186/ISRCTN87225572). Any significant modifications to the study will be updated on this registration.

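### Availability + Size versus baseline has almost no concurrent baseline, so it is largely indirect and model-dependent, and the 6.5% sensitivity figure does not hold for it

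*Protocol article*

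**What the plan says.** - **Study design** describes a stepped wedge "with each of the 19 sites randomly allocated to the time at which they implement each of the two interventions"; the study lasts 25 weeks. On baseline: "Weeks 1 to 4 will comprise the minimum baseline period". On the first roll-out: "From Week 5 until Week 13, two sites a week will implement the first intervention". On the overlap of the two roll-outs: "In Week 14, the 19th site will implement this intervention. From Week 13 until Week 21, two sites a week will implement the second intervention". The 19th site adds Size in Week 22.
- **Background**, last paragraph, Hypothesis 2: "fewer calories will be purchased during the availability + portion size intervention period when compared to the baseline". The same hypothesis also compares the combined period with the Availability period.
- **Data analysis / statistical plan** says that mixed models will "estimate the potential impact of the Availability intervention and the combined Availability + Size intervention compared to baseline". Both comparisons named there are against baseline. Availability + Size versus Availability is not named in that section.
- **Sample size determination** gives one figure: 19 cafeterias, log-scale SD 0.111, one-sided 5% t-test, 80% power, 6.5% reduction (0.067 on the log scale). It does not say which contrast the figure belongs to.
- **Covariates** lists transactions as a definite adjustment and company, day of week, weather, calorie display and events as possible ones. Calendar week and time trend are not in the list.

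**The concern.** What is randomised is the week in which a site crosses over. The protection this gives comes from comparing sites that are in different conditions in the same week. For Availability + Size versus baseline there is almost no such week. The estimate must therefore come either from comparing late weeks with early ones, or from a model that links the two conditions through Availability.

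The first route is open to any drift in sales over 25 weeks. The second is legitimate, but it costs precision and adds an assumption. The article mentions neither. Its Discussion lists only the limits of sales data. A reader could take the combined effect as a directly randomised comparison with the sensitivity given in the sample size section.

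**Working it through.** **1. The plan's own figure.** A one-sample, one-sided t-test on 19 site-level changes with SD 0.111 (noncentral t, 18 df) has 81.2% power at 0.067. The effect detectable with 80% power is 0.0658, a 6.4% reduction. The stated 6.5% therefore reproduces. It implies SE = 0.111/√19 = 0.0255.

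**2. Sites per condition by week** (from Study design):

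| Week | Baseline | Availability | Availability + Size |
|---|---|---|---|
| 1–4 | 19 | 0 | 0 |
| 12 | 3 | 16 | 0 |
| 13 | 1 | 16 | 2 |
| 14 | 0 | 15 | 4 |
| 21 | 0 | 1 | 18 |
| 22–25 | 0 | 0 | 19 |

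Site-weeks:
- Baseline: 4×19 + (17+15+…+1) = 76 + 81 = 157.
- Availability: 19×8 = 152.
- Availability + Size: 475 − 157 − 152 = 166.

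Concurrent overlap:
- Availability + Size with a baseline site: Week 13 only, 2 of 166 (1.2%).
- Availability with a baseline site: 88 of 152 (Weeks 5–13).
- Availability + Size with an Availability site: 90 of 166 (Weeks 13–21).

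These counts do not depend on the order of the sites.

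**3. If week is not modelled.** Fit site and condition effects only, and assume a drift of −0.001 to −0.002 log units per week. The bias in Availability + Size versus baseline is −0.017 to −0.034, which is 25% to 50% of 0.067. With week effects in the model this bias is 0.

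**4. If week is modelled.** With residual variation only and within-site AR(1) correlation 0, 0.3 or 0.6, adding week effects multiplies the variance of this contrast by 8.1, 5.8 or 3.0. At correlation 0 the multiplier is 3.3 for Availability versus baseline and 3.4 for Availability + Size versus Availability. Removing Week 13 altogether hardly changes the relative SE (0.328 to 0.336). So the estimate comes almost entirely through the two adjacent links.

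**5. On the plan's scale.** Generalised least squares with 25 week effects and a site intercept (SD 0.3, assumed). The two step effects vary independently between sites with SD τ, and the Availability component carries on after Size is added (τ 0 to 0.10, assumed). Weekly AR(1) correlation ρ is 0 to 0.6 (assumed). The weekly residual SD is solved so that a site's baseline-to-Availability change has SD 0.111.

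Power = Φ(0.0672/SE − 1.645), where 0.0672 = −ln(0.935). Detectable reduction = 1 − exp(−(1.645 + 0.842)×SE).

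| τ | ρ | SE, each adjacent contrast | SE, combined vs baseline | Ratio | Power at 6.5%, combined vs baseline | Detectable reduction |
|---|---|---|---|---|---|---|
| 0 | 0 | 0.0450 | 0.0705 | 1.57 | 24% | 16.1% |
| 0.10 | 0 | 0.0310 | 0.0458 | 1.48 | 43% | 10.8% |
| 0 | 0.6 | 0.0290 | 0.0424 | 1.46 | 48% | 10.0% |
| 0.10 | 0.6 | 0.0262 | 0.0374 | 1.43 | 56% | 8.9% |

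The combined-contrast SE is 1.5 to 2.8 times the 0.0255 behind the plan's figure (0.0374/0.0255 and 0.0705/0.0255).

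**The case against.** **Calling this a before-after comparison goes too far.** A reader might infer that from the missing overlap. It would hold only if calendar time were left out of the model. With week effects, the contrast is the sum of two links, each with concurrent randomised control. The article names no time term, but it does not list the model terms in full and the full analysis plan is not shown. Omission of time cannot be asserted.

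**A 6.5% effect may be the wrong yardstick for two interventions together.** The article's pilot effects are 7% for Availability and about 8% (Background) or 9% (Discussion) for Size, the latter not statistically significant. If they add on the log scale (an assumption), the combined effect is 0.0726 + 0.0834 = 0.156 to 0.0726 + 0.0943 = 0.167. With SEs of 0.0705 to 0.0458, power is Φ(0.156/0.0705 − 1.645) = 71% to Φ(0.167/0.0458 − 1.645) = 98%. This stands. The documents do not support calling the trial underpowered for the combined effect. It does not remove the wider interval or the stability assumption.

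**Both concurrent contrasts are already declared.** Hypotheses 1 and 2 name them, and the section on reduced portion size gives assessment of the combined effect as an aim. A reader might conclude that the combined contrast should lose confirmatory status. The documents do not require that; it is a debatable trade-off against a stated aim.

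**The magnitudes depend on the model.** This is true. The article does not say that 0.111 is the SD of a site's baseline-to-Availability change, and it calls the value conservative. The values for τ, ρ and the intercept SD are assumed, and a different structure for the site variation would shift the ratio and the power. The week-by-week counts need no assumption.

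**Conclusion.** The concern holds in this form: Availability + Size versus baseline rests almost wholly on indirect, model-dependent evidence, and the article does not say so. The overlap of 2 in 166 site-weeks is exact.

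The contrast is exposed to calendar time if week is not fitted. If week is fitted, it requires that the Availability effect estimated in Weeks 5–13 still applies through Weeks 14–25. Across the assumed ranges in the working, its power at 6.5% never reaches 80%, so the figure under Sample size determination cannot be read as applying to it. Whether the test would succeed depends on how far the true combined effect exceeds 6.5%, which the documents leave open.

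**What to change.** 1. In Data analysis / statistical plan, state that calendar-week effects are fitted and that all three contrasts come from that model.
2. In the same section, name Availability + Size versus Availability, already part of Hypothesis 2, next to Availability versus baseline, and identify these two as the concurrently randomised contrasts.
3. Report Availability + Size versus baseline as the sum of the two coefficients with its own confidence interval. State that there is no concurrent baseline after Week 13 and that a stable Availability effect is assumed.
4. In Sample size determination, say that the 6.5% figure does not apply to this contrast, or restate its detectable effect with the assumptions used.

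The cost is wording plus one linear combination from a single model. Sites, schedule and data collection do not change. The downside is a less favourable stated sensitivity and a wider interval for the combined effect.
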